**X**  Commercial – Provide company name: **Genzyme**

___ Other – Provide source:

___ None

Funding agency deadline for IRB approval: **NA**

Performance sites (see instructions): **UNMC/ The Nebraska Medical Center**

# IRB APPLICATION FOR BIOMEDICAL RESEARCH

SECTION I

**Research Characteristics Checklist**

**Special Populations** (chose all that apply)

__ Minors

___ Pregnant women

___ Fetuses

___ Prisoners (*must attach addendum for Research Involving Prisoners*)

___ Decisionally Impaired

**Special Categories**

___ Genetic Testing (*must attach addendum for Research Involving Genetic Testing*)

___ Gene Transfer (*must submit application to IBC*)

___ Xenotransplantation (*must submit application to IBC*)

**Drugs/Devices** (Choose all that apply)

___ No drugs are used for research purposes

X__ Marketed drugs (*must submit Marketed Drug Form to P&T Committee*)

___ Investigational drug (*must submit Investigational Drug Form to P&T Committee*)

IND # ____________

IND # ____________

___ Investigational Device

IDE # ____________

___ Significant Risk (see Investigator’s Brochure)

___ Non-Significant Risk

**Additional Review Requirements** (Choose all that apply. See individual committee submission requirements)

___ Departmental or other Peer Review Committee

___ Eppley Cancer Center Scientific Review Committee (SRC)

X__ Pharmacy & Therapeutics Committee

___ Institutional Biosafety Committee

___ Radioactive Drug Research Committee

**SECTION II**

**PROTOCOL ABSTRACT**

Title of Protocol: Prospective, Randomized Trial of Thymoglobulin^®^ Induction Therapy for Renal Transplantation: Single vs. Alternate Day Administration

Rabbit anti-thymocyte globulin (rATG, Thymoglobulin^®^) is a polyclonal anti-thymocyte preparation which effectively treats rejection of transplanted kidneys, and is used by many transplant physicians as “induction” therapy at the time of kidney transplantation. Although this preparation is usually administered in a series of divided doses over a course of several days following transplantation, evidence exists that concentrating the administration of a course of rATG at the time of transplantation may confer additional benefits to renal function and possibly increase resistance of the transplanted kidney to calcineurin nephrotoxicity. We hypothesize that a single dose of rATG administered over 24 hours at the time of transplantation will prevent rejection as adequately and safely as the conventional divided dose administration but result in better renal function and graft survival. Testing of this hypothesis will occur via assessment of distinct clinical and immunologic outcomes, outlined in this proposal, in adult recipients of kidney transplants.

The specific primary objectives of this research are to compare the safety and efficacy of single dose (6 mg/kg) rATG induction with the same total dose (6 mg/kg) administered every other day for four doses and to compare calcineurin inhibitor continuation versus calcineurin inhibitor withdrawal. The secondary objectives are to determine the immunological consequences of single dose (6 mg/kg) versus multiple dose administration of rATG; immunological consequences of calcineurin inhibitor continuation versus withdrawal; and to perform a cost analysis of single dose vs. multiple dose administration of rATG.

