**2. Background**

**Describe the background of the study. Include a critical evaluation of existing knowledge, and specifically identify the information gaps that the project is intended to fill.**

Rabbit anti-thymocyte globulin (rATG, Thymoglobulin^®^) is a polyclonal anti-thymocyte preparation which effectively treats rejection of transplanted kidneys, and is used by many transplant physicians as “induction” therapy at the time of kidney transplantation. Although this preparation is usually administered in a series of divided doses over a course of several days following transplantation, evidence exists that concentrating the administration of a course of rATG at the time of transplantation may confer additional benefits to renal function and possibly increase resistance of the transplanted kidney to calcineurin nephrotoxicity. We hypothesize that a single dose of rATG administered over 24 hours at the time of transplantation will prevent rejection as adequately and safely as the conventional divided dose administration but result in better renal function and graft survival. Testing of this hypothesis will occur via assessment of distinct clinical and immunologic outcomes, outlined in this proposal, in adult recipients of kidney transplants.

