**e. Describe briefly the statistical methods used to analyze the data.**

Binomial and numerical outcomes are described using proportions and means, respectively, and are compared using chi-square test or Fisher’s exact test when appropriate and t test, respectively. Graft survival and acute rejection rates are determined using Kaplan-Meier estimates and are compared using log-rank tests. The effects of covariates on the hazard risk of graft survival and acute rejection are evaluated using a Cox proportional hazard model.

A mixed-model for repeated measures is used to compare calculated GFR values to examine the effect of single versus divided-dose rATG on kidney function. A linear mixed-model of repeated measures is used to examine the relationship between the amount of rATG infused at the time of reperfusion and calculated GFR during the follow-up period.

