**b. Does this study involve FDA approved drugs or devices used for off-label purposes?**

Yes, the FDA-approved drug Thymoglobulin will be used off-label.

**1) What is the off-label use?** Off-label use of Thymoglobulin is for immunosuppression induction.

**2) Will the results of this study be used by the manufacturer to support (a) a new indication for the drug, (b) a significant change in the labeling for the drug, or (c) a significant change in the advertising for the drug?** Based on study findings to date, the manufacturer has indicated interest in obtaining a new label indication for Thymoglobulin use as an induction agent in transplantation. Such an additional indication will require a more extensive multi-center trial for which the current study can be viewed as a pilot study.

**3) Does the study involve a route of administration or dosage level, use in a subject population, or other factor that significantly increases the risks (or decreases the acceptability of the risks) associated with the use of the drug?**

No, our study results to date indicate that the risks associated with the administration of the single rATG dose are statistically identical to the risks associated with the administration of the conventional divided-dose.

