**d. What are the specific stopping rules for the research?**

Interim Analysis and Criteria For Halting The Study

During the course of the trial we have monitored for adverse events potentially related to the immunosuppressive agents used in each of the four arms of the study. Interim analyses performed after enrollment of 60 and 140 patients have shown not only generally low and acceptable rates of study-drug related adverse events, but that specifically the rates of adverse events are statistically identical between the study arms.

The originally approved stopping rules for this study have become effectively obsolete, as the study has matured beyond the point where there is any possibility that additional adverse events could exceed the number prescribed as tolerable under the stopping rules algorithm.

While we consider that the safety of the immunosuppressive agents being used in this trial has been well demonstrated, we will continue the policy of stopping enrollment in the study, pending a complete investigation by the Principal, Co-principal, and Secondary investigators, if either of the following should occur:

1. Death of one subject due to an adverse drug reaction
2. A probability of life life-threatening, adverse drug reactions, including pulmonary edema requiring intubation, myocardial infarction, or hypotension requiring significant drug treatment.

Conditions that may warrant termination of the study include, but are not limited to:

- The discovery of an unexpected, serious, or unacceptable risk to patients enrolled in the study.
- The decision on the part of the Investigator to suspend or discontinue testing, evaluation, or development of the clinical program.
- Insufficient adherence to protocol requirements.

Study termination and follow-up will be performed in compliance with the conditions set forth in 21 Code of Federal Regulations (CFR) 312.

**e. Is there a DSMB for this research study?** No.

-If **no**, describe the process of ongoing data analysis:

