**19*.*** **Risk-Benefit Relationship**

**a. What is the relative risk-benefit relationship of the research?**

The primary benefit to patients receiving the single dose of rATG may be an increase in tolerance of the graft. If this occurs, these patients may require reduced levels of maintenance immunosuppression. This would translate into less exposure to potentially toxic side effects and reduced cost.

Further, if patients are able to tolerate conversion to maintenance immunosuppression with sirolimus and low-dose mycophenolate mofetil, this, too would lower exposure to potentially toxic side effects and further reduce cost and inconvenience since management of both tacrolimus and sirolimus require routine blood samples for trough levels. The added risk of another immunosuppressive agent is acceptable since all of these patients require immunosuppression to prevent loss of their graft. Adding low-dose mycophenolate mofetil should provide added protection against the risk of rejection when tacrolimus is discontinued.

**b. What is the relative risk-benefit relationship of the research compared with the risk-benefit relationship of any alternatives?**

Our group recently published an interim analysis of the first 142 patients where we presented evidence that single-dose administration of rATG is safe and associated with improved early renal function when compared to conventional alternate day dosing. Our analysis was unable to detect any differences between groups in relation to rATG-related adverse events, patient and graft survival, acute rejection, or chronic allograft nephropathy rate at six months. However, we did se clear evidence for significantly improved graft function in the group receiving the single rATG dose. A copy of the peer-reviewed published manuscript detailing these findings has been included for the board’s review. It is our belief that this dosing regimen offers the subject a favorable risk-benefit relationship when compared to conventional divided-dose administration.

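### The hypothesis says single-dose rATG is no worse on rejection and safety, but item 10e names only tests of difference, and a failure to detect differences is already reported as identical risk

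*Protocol*

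**What the plan says.** The Protocol Abstract states the hypothesis: a single dose "will prevent rejection as adequately and safely as the conventional divided dose administration but result in better renal function and graft survival". Item 2 (Background) repeats it, and both places say that it will be tested on clinical and immunologic outcomes. Primary goal 1 in item 1 is to compare safety and efficacy of the two rATG schedules. Safety profile and acute rejection are listed as secondary endpoints in item 10.

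Item 10e gives the methods. Binomial and numerical outcomes "are described using proportions and means, respectively, and are compared using chi-square test", with Fisher's exact test and the t test as companions. For time-to-event outcomes: "Graft survival and acute rejection rates are determined using Kaplan-Meier estimates and are compared using log-rank tests". It adds: "The effects of covariates on the hazard risk of graft survival and acute rejection are evaluated using a Cox proportional hazard model". Item 10e attaches no margin or confidence-limit criterion to any of these.

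Three items report results so far:

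- Item 19b, on the published interim analysis of the first 142 patients: "Our analysis was unable to detect any differences between groups in relation to rATG-related adverse events, patient and graft survival, acute rejection".
- Item 15d, on the interim analyses at 60 and 140 patients: "the rates of adverse events are statistically identical between the study arms". It goes on to call the safety of the agents well demonstrated.
- Item 11b(3), answering No to whether dosage or another factor significantly raises risk: the risks of the single dose are "statistically identical to the risks associated with the administration of the conventional divided-dose".

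**The concern.** The hypothesis has two halves that need different evidence. Better renal function and graft survival is a superiority claim, and tests of difference suit it. The other half, that the single dose "will prevent rejection as adequately and safely as the conventional divided dose administration", says the single dose is no worse. A chi-square, Fisher or log-rank test takes no difference as its null hypothesis. A non-significant result leaves that null standing but does not establish it. The smaller the sample, the more readily non-significance occurs, so the test rewards imprecision.

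The document itself already takes this step. Item 19b words the interim result correctly. Items 11b(3) and 15d turn results of this kind into equality of risk, and 11b(3) rests its answer to the IRB on it. Item 15e says there is no DSMB, so the IRB relies on this wording. Item 15e(1) still foresees a formal analysis of the induction phase once accrual is complete, and the same step could be repeated there.

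**Working it through.** **Side by side.** Item 15e(1) says that the 140-subject interim analysis was published. Item 19b describes the published interim analysis, giving 142 patients. These appear to be the same analysis. Item 19b says no difference was detected; item 15d says the rates are identical. The second statement does not follow from the first.

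**The plan's own figure.** Item 3b cites 200 subjects as allowing for 10% drop-out: 180 / (1 − 0.10) = 200, which reproduces. The base of 180 cannot be reproduced, because alpha, power, effect size and control rate are in an attachment that is not shown.

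**Inputs.**

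- Interim: 142 patients (item 19b), about 142 / 2 = 71 per induction arm if split evenly.
- Design: 180 patients (item 10a), 1:1:1:1 allocation (Protocol Abstract), so 90 per induction arm.
- With 10% loss from 180: 162 patients, 81 per arm.
- Event rates and margins: not given in the document, so assumed and shown as ranges.

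**Step 1: what equal observed rates leave open.** The 95% half-width for the difference is 1.96 × √(2p(1−p)/n). Example at p = 0.10, n = 71: 1.96 × √(0.18/71) = 1.96 × 0.0503 = 9.9 points.

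| Assumed rate in both arms | 71 per arm | 81 per arm | 90 per arm |
|---|---|---|---|
| 5% | ±7.2 | ±6.7 | ±6.4 |
| 10% | ±9.9 | ±9.2 | ±8.8 |
| 15% | ±11.7 | ±11.0 | ±10.4 |
| 20% | ±13.2 | ±12.3 | ±11.7 |

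**Step 2: how often a real excess goes undetected.** This is the power of a two-sided 5% test for a true 10-point excess, Φ[(δ − 1.96√(2p̄(1−p̄)/n)) / √((p₁q₁ + p₂q₂)/n)]. Example for 10% versus 20%, n = 71: (0.100 − 0.1175)/0.0593 = −0.29, so power is 0.38.

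| Lower rate | 71 per arm | 90 per arm |
|---|---|---|
| 5% | 51% | 61% |
| 10% | 38% | 47% |
| 15% | 32% | 39% |
| 20% | 28% | 34% |

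At an assumed 10% rate, a true doubling is therefore non-significant about 62% of the time at 71 per arm (1 − 0.384) and about 53% at 90 per arm (1 − 0.467).

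**Step 3: what a confidence-limit criterion could deliver.** With equal true rates and one-sided 0.025, non-inferiority power is Φ[margin/√(2p(1−p)/n) − 1.96]. Example at 90 per arm, p = 0.10, 10-point margin: 0.10/0.0447 − 1.96 = 0.28, so power is 0.61.

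| Assumed rate, 90 per arm | 5-point margin | 10-point margin | 15-point margin |
|---|---|---|---|
| 5% | 34% | 87% | >99% |
| 10% | 20% | 61% | 92% |
| 15% | 15% | 47% | 81% |
| 20% | 13% | 39% | 71% |

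All of this uses normal approximations for simple proportions and ignores censoring.

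**The case against.** Item 10e asks only for a brief description. A detailed 2005 power analysis is attached but not shown, and an SAP may exist; either could hold a margin. Rejection and safety are secondary endpoints. The primary endpoints, nephropathy and renal function, serve the superiority half. Goal 1 speaks of comparing and makes no equivalence claim, and item 11b(2) says the study can be viewed as a pilot for a larger trial. Items 11b(3) and 15d are answers on an IRB form and do not form part of the analysis plan. Arm-level results on 142 patients are already published, so a margin set now is not independent of the data.

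Most of this stands, and it rules out stronger readings that a reader might infer:

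- **That no margin exists.** This cannot be known from the protocol alone.
- **That the plan will declare equality whenever a test is non-significant.** No such rule is written, and item 10e also plans proportions and Kaplan-Meier estimates.
- **That rejection has been declared identical.** The equality wording covers risks and adverse-event rates. For rejection, item 19b says only that no difference was detected.

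The objection does not rescue the equality wording. An unseen SAP cannot correct what this document tells the IRB, and pilot status favours estimates with intervals over claims of equality. The methods that are named still do not address the half of the hypothesis that the document says will be tested.

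**Conclusion.** The point holds as a mismatch between claim and method, together with an unsupported inference already on the page. The logic does not depend on any assumed rate. The rates give only its size: at assumed event rates of 5 to 20%, equal observed results at the interim sample size leave excesses of about 7 to 13 points open, and at 90 per arm about 6 to 12 points.

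A reader might also infer that a no-worse-than conclusion is out of reach at this size. The figures do not support that in general. At 90 per arm with a 10-point margin, power runs from 87% at a 5% rate to 39% at a 20% rate, and it also depends on the margin. Nor do the figures show that the single dose carries more risk; they show only that absence of excess risk has not been demonstrated.

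The matter should be corrected before the final induction-phase analysis, but it does not affect the primary renal-function comparison.

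**What to change.** **Item 10e.** State that the no-worse-than half of the hypothesis is judged on the single-minus-divided difference in biopsy-proven acute rejection and key adverse events, each with a 95% confidence interval, and that a non-significant test will not be read as equality. Then, for the margin:

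- If one already exists in the 2005 power analysis or the SAP, cite it and apply it to the upper confidence limit.
- If one is set now, justify it from external evidence and declare that it was set after the interim results were published.
- If none is used, report the interval and say which excess is not excluded.

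**Items 11b(3) and 15d.** Replace the equality wording with a statement that no statistically significant difference was detected, give event counts per arm and the confidence interval, and base the answer on increased risk on those figures.

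**Cost.** A few sentences and one interval per endpoint, with no change to enrolment, procedures or treatment. The price is a more modest conclusion on rejection and safety: with a 10-point margin and 90 per arm, power is about 87, 61, 47 and 39% at assumed rates of 5, 10, 15 and 20%.

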**PURPOSE OF THE STUDY AND THE BACKGROUND (1-2).**

**1. Purpose of the Study**

**What are the specific scientific objectives (aims) of the research?**

Primary goals:

1. Compare the safety and efficacy of single-dose (6 mg/kg) rATG induction with the same total dose (6 mg/kg) administered every other day for four doses (divided-dose).
2. Compare standard renal transplantation outcome measures in patients converted approximately 6 months post-transplantation from maintenance immunosuppression with sirolimus and tacrolimus to sirolimus and low-dose mycophenolate mofetil.

Secondary goals:

1. Determine the immunological consequences of single-dose (6 mg/kg) versus divided-dose administration of rATG
2. Determine the immunological consequences of calcineurin-inhibitor (CNI) continuation versus CNI withdrawal.
3. Perform a cost analysis of single-dose vs. divided-dose administration of rATG.

**2. Background**

**Describe the background of the study. Include a critical evaluation of existing knowledge, and specifically identify the information gaps that the project is intended to fill.**

Rabbit anti-thymocyte globulin (rATG, Thymoglobulin^®^) is a polyclonal anti-thymocyte preparation which effectively treats rejection of transplanted kidneys, and is used by many transplant physicians as “induction” therapy at the time of kidney transplantation. Although this preparation is usually administered in a series of divided doses over a course of several days following transplantation, evidence exists that concentrating the administration of a course of rATG at the time of transplantation may confer additional benefits to renal function and possibly increase resistance of the transplanted kidney to calcineurin nephrotoxicity. We hypothesize that a single dose of rATG administered over 24 hours at the time of transplantation will prevent rejection as adequately and safely as the conventional divided dose administration but result in better renal function and graft survival. Testing of this hypothesis will occur via assessment of distinct clinical and immunologic outcomes, outlined in this proposal, in adult recipients of kidney transplants.

The primary mechanism of action of rATG in vivo, determined by primate studies, is likely cell death via apoptosis. At high doses, cell death occurs in both the bloodstream and in lymph nodes, but not in the thymus. Based on their primate data, Preville, et al,^1^ surmised that lymphocyte depletion in tissues may correlate with peak levels of Thymoglobulin rather than the total dose given. Cell surface markers are down-modulated, in a dose-dependent fashion, on lymphocytes that have escaped deletion. In humans, Thymoglobulin^®^ induces short-term depletion of peripheral lymphocytes, and a long-term decrease in the CD4:CD8 ratio of T-cells in the periphery. Studies of immune cell reconstitution following chemotherapy or treatment of AIDS have revealed that restoration of the CD4+ T-cell compartment comes largely from the thymus. Restoration of the CD8+ compartment comes mainly from proliferation of cells present in the peripheral immune system, which likely explains the changes in CD4:CD8 ratio that are seen following Thymoglobulin. In addition to the changes in the CD4:CD8 ratios, patients treated with Thymoglobulin also exhibit a long-term increase in the proportion of CD8+ CD57+ T-cells. These T-cells represent a replicatively senescent population prone to activation-induced cell death, and are associated with improved graft survival in recipients of kidney transplants.

Although most centers administer rATG over several days, a few centers have reported their experience with a single bolus of anti-thymocyte globulin (ATG). Three centers used ATG in a single bolus of 9 mg/kg without untoward side effects. In these reports, a single bolus of ATG was compared to no induction therapy, and therefore no information can be gleaned as to potential differences between single-dose and divided-dose administration. Agha, et al,^2^ reported results in which a single dose of Thymoglobulin at 3 mg/kg was followed by 2 doses at 1.5 mg/kg. He compared this regimen retrospectively to the standard regimen of 1.5 mg/kg for 7-10 days. Interestingly, a more prolonged lymphocyte depletion was observed with the “short course” regimen containing the higher initial dose. Swanson, et al,^3^ reported the use of very large dose Thymoglobulin^®^ administered in a regimen of 2.5 mg/kg/day for a total dose of 20 mg/kg. Absolute lymphocyte counts at 6 months were similar to those observed by Agha, et al for patients receiving the “short course” induction therapy. Although the maintenance immunosuppression regimens were quite different (rapamycin versus cyclosporine, azathioprine, and prednisone), a comparison of these studies suggests that large total doses of Thymoglobulin, given in several smaller doses, may be of no greater efficacy than smaller total doses given as larger individual boluses. These findings may relate to the development of anti-rabbit antibodies. Preville, et al,^1^ noted that in primates Thymoglobulin antibodies were totally neutralized by anti-Thymoglobulin antibodies at 11 days post-initiation of treatment. In humans, Regan, et al,^4^ reported that 70% of patients developed anti-Thymoglobulin antibodies by 3 weeks post-initiation of multi-dose therapy. Since repeated administration of an antigen is the best way to initiate the formation of antibodies, a large single dose of Thymoglobulin may result in decreased sensitization and improved efficacy.

Given the long-term effects of rATG, administration of this agent may impact a patient’s requirements for maintenance immunosuppression. Therefore, if a single-dose of rATG is more efficacious than multiple, low doses of rATG, patients receiving this single dose may require less maintenance immunosuppression. To test this hypothesis, patients receiving single-dose or divided-dose rATG will also be randomized to either continue receiving sirolimus and tacrolimus maintenance immunosuppression or be converted after approximately 6 months to sirolimus and low-dose mycophenolate mofetil. Although the combination of tacrolimus and sirolimus has rendered excellent prophylaxis against rejection at our institution, this combination is not tolerated by all patients, especially with regard to side effects such as leukopenia, anemia, and hyperlipidemia.

In order to assess maintenance immunosuppression without the toxicities associated with calcineurin inhibitors on renal allograft function, monotherapy with sirolimus was initially considered for subjects randomized to two of the treatment groups. Subjects who were rejection-free at six months post-transplant would be eligible to change to this regimen. However, in one small study reported by Rao et al^5^, 29 primary kidney transplant patients received induction therapy with Campath-1H followed by monotherapy with sirolimus. In this group, 8 patients (28%) had rejection. Compared to Thymoglobulin, Campath-1H is a more potent induction agent, and thus our protocol may have a rejection rate in excess of 28%. If this were to be the expected rate of rejection, it would be unacceptable.

This investigator has also had numerous discussions with other members of the kidney transplant community who expressed concern that monotherapy with sirolimus may not provide enough protection against rejection. Instead, dual-therapy with sirolimus and low-dose mycophenolate mofetil would achieve the same goal of our original proposal, namely, elimination of chronic use of calcineurin inhibitors while still providing adequate protection against rejection. Finally, patients receiving this dual-therapy may be less susceptible to certain viral infections that are particularly problematic in renal transplant patients (especially CMV and BK virus).

